**Fig. 4 Fig4:**
[figure not shown]
EIT-guided individualized PEEP titration. *Paw* airway pressure, *Pplat* plateau airway pressure, *PEEP* positive end-expiratory pressure, *V*_*T*_ tidal volume normalized for adjusted body weight, *RR* respiratory rate, *RM* the ventilator-driven alveolar recruitment maneuver

In the Cstat-iPEEP group, patients’ iPEEP is obtained through the following procedure (Fig. 5):
The first RM (RM1) is performed 5 min after intubation.Limit the peak airway pressure to lower than 55 cmH_2_O.*V*_*T*_ is fixed to 7ml/kg (predicted body weight, PBW), I: E to 1:1, respiratory rate to 12–15 breaths/min.Titration procedure: Immediately after the establishment of pneumoperitoneum, PEEP titration is started. Initial PEEP is set to 5 cmH_2_O. PEEP is increased at steps of 2 cmH_2_O, and each PEEP level is sustained for 3 min, during which Cstat is calculated (in accordance with the formula: Cstat = V_T_ /Plat-PEEP). We end the titration process the moment the calculated Cstat displays a downward trend and choose its previous PEEP (the PEEP that maximizes Cstat) as the optimal PEEP for this patient.The upper limit of PEEP is set to 20 cmH_2_O.After the ideal PEEP is obtained, we perform the second RM2.The third RM3 is performed before extubation.

**Fig. 5 Fig5:**
[figure not shown]
Individualized PEEP titrated by optimal Cstat. *Cstat* static lung compliance, *PEEP* positive end-expiratory pressure, *iPEEP* individualized positive end-expiratory pressure, *RM* the ventilator-driven alveolar recruitment maneuver

### Study endpoints

The primary endpoint of the study is the amount of calculated atelectasis, corresponding to the percentage of collapsed lung mass, which is obtained through the following steps. The baseline lung volume and its associated parameters of all patients are measured before and after anesthesia induction by Drager’s EIT. Immediately after extubation and 2 h postoperation, the proportion taken up by collapsed lung mass is measured by EIT. The amount of atelectasis is calculated via dividing the area occupied by non-ventilated lung mass by baseline lung volume.

Secondary endpoints consist of the value of individualized PEEP, oxygenation index (PaO_2_/FiO_2_), respiratory parameters, blood gas analysis indicators, anesthesia-associated parameters, and hygienic index.
Oxygenation index: At before intubation (T0), after the third RM and before extubation (T1), arterial blood is drawn, blood gas analysis is performed, and oxygenation index is calculated.Respiratory parameters: Every 5 min, RR, VT, Ppeak, Pplat, and PEEP are recorded.Blood gas analysis indicators: At before intubation (T0), after the third RM and before extubation (T1), arterial blood is drawn and blood gas analysis is performed.Anesthesia-associated parameters: hemodynamic parameters, recovery time, anesthetic dosage, and occurrence of hypoxemia are recorded constantly.Tertiary outcomes: length of ICU stay, length of hospital stay, costs of treatment, postoperative complications, and other adverse events are recorded.We define PPCs as follows:Mild respiratory failure: PaO_2_/FiO_2_ < 300 or SpO_2_<90%, measured after at least 10 min of breathing room air, but could be alleviated by inhaling supplementary oxygen of 2L/min, hypoventilation excluded.Moderate respiratory failure: PaO_2_/FiO_2_ < 300 or SpO_2_<90%, measured after at least 10 min of breathing room air, but could be alleviated only by inhaling supplementary oxygen>2L/min, hypoventilation excluded.Severe respiratory failure: requiring noninvasive or invasive mechanical ventilation, excluding hypoventilation due to the use of narcotics.ARDS (according to Berlin definition).Bronchospasm (newly detected expiratory wheezing, responding to bronchodilators).New pulmonary infiltrates (new monolateral or bilateral infiltrates demonstrated by chest X-ray, without other clinical signs.)Pulmonary infection (new or progressive radiographic infiltrate plus at least two of the following: requirement of antibiotic treatment, tympanic temperature >38°C, leukocytosis, or leukopenia [white blood cell count <4000 cells/mm^3^ or > 12,000 cells/mm^3^], and/or purulent sputum).Aspiration pneumonitis (respiratory failure resulting from inhalation of regurgitated gastric contents).Pleural effusion (one of the following demonstrated by chest X-ray: blunting of the costophrenic angle, loss of the sharp silhouette of the ipsilateral hemidiaphragm in the upright position, evidence of adjacent anatomical structures displacement, or [in supine position] a hazy opacity in one hemithorax with preserved vascular shadows).Atelectasis (lung opacities with a shift of the hilum, mediastinum, or hemidiaphragm toward the affected area, along with compensatory overdistension in the adjacent nonatelectatic lung).Cardiopulmonary edema (clinical signs of congestion, including dyspnea, edema, rales, and jugular venous distention, with chest X-ray demonstrating an increase in vascular markings and diffuse alveolar interstitial infiltrates).Pneumothorax (air in the pleural cavity, without vascular bed around the visceral pleura).

Patients conforming to one of the above conditions are deemed as positive for PPCs.

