**Methods:**

A total number of 140 obese patients with BMI ≥ 32.5kg/m^2^ undergoing elective laparoscopic gastric volume reduction and at moderate to high risk of developing PPCs will be enrolled and randomized into the optimal static lung compliance-directed iPEEP group and EIT titration iPEEP group. The primary endpoint will be pulmonary atelectasis measured and calculated by EIT immediately after extubation and 2 h after surgery. Secondary endpoints will be intraoperative oxygenation index, organ dysfunction, incidence of PPCs, hospital expenses, and length of hospital stay.

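### The PPC definition is non-monotone: a new infiltrate with fever alone or purulent sputum alone meets neither infiltrate-based item, while the same infiltrate with no sign counts as a PPC

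*Protocol article*

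**What the plan says.** The Study endpoints section of the protocol article defines PPCs by a list of twelve conditions and closes with the scoring rule: "Patients conforming to one of the above conditions are deemed as positive for PPCs".

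Two of the twelve are built on a radiographic infiltrate alone or with signs of infection:

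- The infiltrate item: "New pulmonary infiltrates (new monolateral or bilateral infiltrates demonstrated by chest X-ray, without other clinical signs".
- The infection item: "Pulmonary infection (new or progressive radiographic infiltrate plus at least two of the following: requirement of antibiotic treatment, tympanic temperature >38°C, leukocytosis, or leukopenia", where the list is completed by "white blood cell count <4000 cells/mm^3^ or > 12,000 cells/mm^3^], and/or purulent sputum". This gives four distinct items: antibiotic requirement, temperature, abnormal white count and purulent sputum.

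The standing of PPCs differs between sections. The abstract states: "Secondary endpoints will be intraoperative oxygenation index, organ dysfunction, incidence of PPCs, hospital expenses, and length of hospital stay". The Study endpoints section has: "Tertiary outcomes: length of ICU stay, length of hospital stay, costs of treatment, postoperative complications, and other adverse events are recorded". The Background section includes reduction of PPC incidence in the non-inferiority hypothesis.

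**The concern.** The infiltrate item stops counting as soon as a further clinical sign appears, but the infection item starts counting only at two items. Nothing in the list covers the step between, and no text sends such a patient back to the infiltrate item.

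Adding one sign of infection to a bare infiltrate can therefore turn a PPC-positive patient negative, and a second item turns the patient positive again. A complication definition should not lose an event when a finding is added to it.

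At stake is the PPC incidence. It can be under-counted if assessors follow the text strictly, or scored inconsistently if some follow the text and others follow what they take to be the intent.

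**Working it through.** There is no planned figure to reproduce, because the point concerns a classification rule and not an error rate, a margin or a sample size. The check is to apply the two definitions to every possible patient.

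**Inputs** (all from Study endpoints): the infiltrate item, the four infection items with their threshold of two, and the closing scoring rule.

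**Set-up.** Take a patient with a new infiltrate and none of the other ten conditions. Each infection item is present or absent, so there are 2^4 = 16 patterns: 1 with no item, 4 with exactly one, and 6 + 4 + 1 = 11 with two or more.

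**Two readings.** The article does not define clinical signs, so both were applied:

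- Broad: all four items are clinical signs.
- Narrow: only temperature and purulent sputum are. A white count is a laboratory result and an antibiotic requirement is a treatment decision.

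| Items present with the new infiltrate | Infiltrate item | Infection item | Score |
|---|---|---|---|
| None | met | not met | positive |
| Temperature >38°C only | not met | not met | **negative** |
| Purulent sputum only | not met | not met | **negative** |
| Abnormal white count only | broad: not met; narrow: met | not met | broad: **negative**; narrow: positive |
| Antibiotic requirement only | broad: not met; narrow: met | not met | broad: **negative**; narrow: positive |
| Two or more (11 patterns) | depends on pattern | met | positive |

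**Result.** On the broad reading 4 of 16 patterns are negative on both items; on the narrow reading 2 of 16 are. Fever alone and sputum alone fall in the gap on both. These are counts of patterns, not of patients: the patterns are not equally likely, and the documents do not say how likely each is.

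**Do the other ten conditions close the gap?** Not in general. The three grades of respiratory failure, ARDS, bronchospasm, aspiration pneumonitis, pleural effusion, atelectasis with shift, cardiopulmonary edema and pneumothorax each need findings other than an infiltrate with one infection item. Some one-sign patients will meet one of them and be scored positive that way. A patient with an infiltrate, isolated fever and adequate oxygenation need not.

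**After the fix.** If the infiltrate item covers any new infiltrate that does not meet the infection criteria, the 1 + 4 = 5 patterns with no item or one item fall under it, the other 11 fall under infection, and none is left out. The score no longer depends on how clinical signs is read.

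**The case against.** **The strict reading is not the only one.** The qualifier on the infiltrate item may be meant to separate a bare radiographic finding from the fuller diagnoses listed beside it. An assessor who reads it so would score the one-sign patient positive. This is plausible, and it means the practical harm may be inconsistent scoring rather than a systematic undercount. It does not remove the point: the text as written scores the patient negative, and no other passage corrects it.

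**The gap is certain only for two items.** This stands. For an isolated white count or antibiotic requirement it depends on an undefined term.

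**The consequence is limited.** This also stands. The primary endpoint is EIT-measured collapse, the sample size rests on it, and the same PPC rule applies to both arms.

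A reader might infer more than the documents support:

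- *That several patients would be lost from the count.* The Background section cites an 18% incidence in obese patients, and one could multiply it by 140. That figure is background literature, not a planning rate. The share of PPCs resting on an infiltrate alone and the frequency of each sign are not given, so any count would be an assumption.
- *That the arms would be affected differently.* Antibiotic requirement is a treatment decision, and the Objectives and design section describes assessor blinding only. But an isolated antibiotic requirement is in the gap only on the broad reading, and nothing in the article shows that the misclassification would differ by arm.
- *That the negative patient is always the sicker one.* An isolated postoperative fever is non-specific. The defect is that the rule is incoherent, not that it ranks patients by severity in reverse.

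**Conclusion.** The point holds in a limited form. The stated PPC rule is non-monotone. With no other PPC condition present, a new infiltrate is positive with no sign, negative with fever alone or purulent sputum alone, and positive with two or more items. For an isolated abnormal white count or antibiotic requirement, the result depends on what counts as a clinical sign.

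This is not a detail left to another document. The article gives the component definitions and the scoring rule in full, and the rule gives an incoherent answer when followed.

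The effect is confined to PPC incidence, an endpoint of secondary or tertiary rank that nevertheless forms part of the stated hypothesis. The primary endpoint and the sample size are unaffected. No numerical size can be given from the documents. The conclusion rests only on the literal wording and on the patient meeting none of the other ten conditions.

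**What to change.** In the PPC list, replace the qualifier that closes the infiltrate item (the exclusion of other clinical signs) by the condition that the pulmonary infection criteria are not met. Every new infiltrate then falls under one of the two items. Apply the amended definition to all patients, including those already enrolled, before any unblinded analysis, and record the change with its date.

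The sponsor should first confirm that the individual signs and the chest X-ray findings are recorded after surgery. The section on blinding and data collection mentions laboratory results and postoperative clinical status in general terms. However, Study visits and data collection names body temperature and routine blood tests only under preoperative indicators, and its postoperative list speaks only of the presence of complications and adverse events. Table 1 is not visible. If only the final PPC verdict is kept, patients already enrolled could not be rescored without going back to source records.

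The cost is one phrase. The downside is a slightly higher PPC count and a small change in wording from the current definition. No patient's care changes.

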### Study visits and data collection

We visit patients preoperatively, intraoperatively, and postoperatively on postoperative days 1 and 3 and at discharge (Table 1). At all the above-listed points in time, patients’ data are collected and recorded.
Preoperative indicators: gender, age, weight, height, body mass index, smoking status, assessment of difficult airways, ASA grade, heart rate, blood pressure, body temperature, blood routine, blood biochemistry, coagulation function, and other past histories.Intraoperative indicators: heart rate, blood pressure, pulse oxygen saturation, bispectral index, respiratory parameters, PEEP settings, all data measured by EIT, transfusion of blood products, volume of fluids and dosage of drugs administered throughout the duration of anesthesia (e.g., crystalloid fluid, colloid fluid, analgesic drugs, sedative drugs, muscle relaxants, vasoactive drugs), urine output, duration of operation (from incision to closure), etc.Postoperative indicators: duration of ICU treatment, length of hospital stay, hospitalization expenses, presence of complications, and adverse events.

**Table 1 Tab1:**
[figure not shown]
Standard protocol items: time schedule of enrollment, interventions, and assessments

*PNP* pneumoperitoneum period, *POD1* postoperative day 1, *POD3* postoperative day 3, *PEEP* positive end-expiratory airway pressure, iPEEP individual PEEP, *RM* recruitment maneuver, *EIT* electrical impedance tomography, *PNP* pneumoperitoneum, *PPCs* postoperative pulmonary complications, *POD* postoperative day, *ICU* intensive care unit

### Study dropouts

As participation in the study is voluntary, all subjects are free to withdraw their consent to participate in the trial at any time and for any reason without any further treatment or any consequences. Moreover, participation of any subjects could be terminated by an investigator at any time, if he or she believes it is in the best interest of the subject. We shall document the reasons and circumstances of the study discontinuation in the CRF.

### Sample size calculations

The primary endpoint of this study is the ratio of collapsed lung mass to normal lung tissue, which is measured and automatically calculated via using EIT before anesthesia and immediately after endotracheal extubation. According to our pre-experimental results of this study, the lung collapse area in the Cstat-PEEP group was 6.5%, while that in the EIT-PEEP group was 6.2%. We apply a noninferiority test. We hypothesize that compared with the ratio of lung collapse area in the EIT-PEEP group, the ratio of lung collapse area in the Cstat-PEEP group will increase by no more than 2% (i.e., the ratio of lung collapse area in Cstat-PEEP group within 8.2% is non-inferior). We choose a two-sided significance level of 0.025 (*α*) and *β*= 0.2, with a power of 80%. Using the PASS 11.0 software, a sample size of 64 is calculated for each group. Taking a 10% dropout rate in patients’ follow-up into account, a final sample size of 70 is required for each group.

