### Statistical analysis

After completing the trial, the research team will collaborate with medical statisticians to analyze the data. Statistical analysis will be performed on the basis of intention to treat. SPSS 20.0 software will be used for analysis. The majority of data will be collected and recorded onto the CRF. Before analyzing the data, the pattern of missing data will be evaluated. Analyzation of graphics and data acquired from the EIT machine will be executed by a computer expert familiar with machine principles. Kolmogorov-Smirnov analysis will be used to detect the distribution of all the data. Normally distributed data will be expressed by the mean and standard deviation (SD), while skewed data will be expressed by their median and interquartile range. Unpaired *t* test will be used for univariate analysis of normally distributed data. Pearson correlation test will be employed to test the correlation between two variables. Mann-Whitney *U* test and Wilcoxon signed-rank test will be applied for skewed data. Categorical variables will be assessed by Fisher’s exact test, chi-square tests, or relative risk, if appropriate. 95% CI will be employed to express statistical uncertainty. *P* value <0.05 shall be regarded as significant.

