## Discussion

This trial is sufficiently powered to test the hypothesis that an individualized PEEP titrated by maximizing Cstat is not inferior to individualized PEEP determined by EIT in terms of lowering the proportion of collapsed lung tissue, for obese patients. The result will prove that the method of best Cstat titration iPEEP is simple and effective in clinical practice.

According to a population-based study, in 2014, approximately 10.8% of men and 14.9% of women are obese globally [13]. In obese patients, the respiratory compliance is further limited by the cephalic movement of the diaphragm. In addition, the FRC and alveolar ventilation volume of obese patients are much lower than their non-obese counterparts. The incidence of atelectasis in obese patients under general anesthesia is as high as 90% [14]. In obese patients under general anesthesia and mechanical ventilation, the proportion of normal ventilated lung tissue drops from 71 to 50%, while the proportion of insufficiently ventilated lung mass increases from 28 to 39%, and the proportion of non-ventilated lung tissue elevates from 1 to 11%. In sharp contrast, the proportion of atelectatic lung mass is only 3% in normal weight patients under general anesthesia and mechanical ventilation [15].

Because airway pressure required to keep lung units from collapsing is much lower than the pressure needed to recruit atelectatic lung units, recruitment maneuver could significantly improve ventilation. Applying PEEP after a successful recruitment maneuver could prevent the rapid reformation of atelectasis, especially when the fraction of inspired oxygen is as high as 100% [16]. Applying PEEP alone alleviates the reduction of end-expiratory lung volume and lung elastance imposed by pneumoperitoneum on obese patients, but fails to reduce an atelectatic fraction of the lung tissue [17]. Compared to PEEP applied alone, the combination of PEEP and recruitment maneuver leads to greater enhancement in lung elastance and results in lower airway pressure as well as resistance in obese patients undergoing laparoscopic surgery.

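### The alpha used to size the non-inferiority test (two-sided 0.025) does not match the 95% CI and P<0.05 of the analysis section; separately, 70 per group falls one short of 64 after 10% dropout

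*Protocol article*

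**What the plan says.** All places are in the protocol article.

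- **Sample size calculations.** The design is declared as "We apply a noninferiority test". The pilot values are that "the lung collapse area in the Cstat-PEEP group was 6.5%, while that in the EIT-PEEP group was 6.2" per cent, and the margin is an increase of 2 percentage points, so that up to 8.2% in the Cstat group counts as non-inferior. The error rate is given as "We choose a two-sided significance level of 0.025", with 80% power. The software returns 64 per group. After an allowance for 10% dropout, "a final sample size of 70 is required for each group". No SD is given, and the text does not say which true difference was entered.
- **Statistical analysis.** After a general list of tests, the section says that "95% CI will be employed to express statistical uncertainty" and that a P "value <0.05 shall be regarded as significant". Neither statement gives a sidedness or is tied to the non-inferiority margin.
- **Discussion.** "This trial is sufficiently powered to test the hypothesis" that Cstat titration is not inferior to EIT titration for the proportion of collapsed lung.

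**The concern.** A non-inferiority conclusion depends on one tail only: whether the upper confidence limit for Cstat minus EIT lies below the margin. The alpha therefore decides which limit is compared with 2 points. The two sections point to different limits, the upper end of a 97.5% interval or of a 95% interval. A result close to the margin could pass under one and fail under the other, and the text would support either choice after the data are seen. The trial was still recruiting when the article appeared, so this can be settled in advance.

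The dropout step raises a smaller question: whether 70 enrolled per group yields the 64 evaluable patients that the calculation requires.

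**Working it through.** **Inputs from Sample size calculations:** margin 2 points; pilot difference 6.5 − 6.2 = 0.3 points; power 80%; 64 per group, raised to 70 for 10% dropout. **From Statistical analysis:** 95% CI, P<0.05, unpaired t test for normally distributed data. **Not given:** the SD and the true difference entered. Both are treated below as assumptions.

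**1. What each statement means in the deciding tail**

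| Statement | One-sided error | Matching two-sided CI |
|---|---|---|
| Two-sided 0.025 (sample size), read literally | 0.025 / 2 = 0.0125 | 97.5% |
| 95% CI (analysis) | 0.05 / 2 = 0.025 | 95% |
| P<0.05 (analysis), ordinary two-sided reading | 0.025 | 95% |
| P<0.05, only if applied to a one-sided non-inferiority P value | 0.05 | 90% |

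The conflict is 0.025 / 0.0125 = twofold. It becomes 0.05 / 0.0125 = fourfold only on the last row.

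**2. Can the 64 be reproduced?** Let δ = 2 − true difference. Power is the probability that a noncentral t variable with 2n − 2 degrees of freedom and noncentrality δ / (SD·√(2/n)) exceeds the one-sided critical value. Solving for the SD that gives 80% power at n = 64:

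| Alpha used for sizing | SD if true difference 0.3 | SD if true difference 0 |
|---|---|---|
| One-sided 0.025 | 3.41 | 4.01 |
| Literal two-sided 0.025 (0.0125 per tail) | 3.09 | 3.63 |

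Worked example at one-sided 0.025: SD 3.4 with difference 0.3 gives 1.7 / 3.4 = 0.50, and SD 4.0 with difference 0 gives 2 / 4 = 0.50. The normal formula is n = 2 × (1.960 + 0.842)² / 0.50² = 62.8, so 63; the t-based value is 64. At the literal alpha, SD 3.1 with difference 0.3 gives 64 (normal) or 65 (t). The 64 can thus be reached under either alpha with an ordinary-looking SD, so it cannot identify the alpha.

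**3. Power of the planned 95% CI analysis, if 64 was correctly sized**

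| How 64 was sized | Power at n = 64 | Power at n = 63 |
|---|---|---|
| One-sided 0.025 (standardised distance 0.50) | 80.1% | 79.5% |
| Literal two-sided 0.025 | 87.1% | 86.6% |

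In the second row the higher power comes with twice the per-tail error used for sizing.

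**4. How far the two limits lie apart.** As an illustration with an assumed SD of 3.4 and 64 per group, the standard error is 3.4 × √(2/64) = 0.601. With normal quantiles, non-inferiority needs an observed difference below 2 − 1.960 × 0.601 = 0.82 points under the 95% CI, or below 2 − 2.241 × 0.601 = 0.65 points under the 97.5% CI. The gap is about 0.17 points. For SDs from 3.1 to 4.0 it is 0.15 to 0.20.

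**5. Dropout.** 64 / 0.9 = 71.1, so 72 per group. The stated 70 matches 64 × 1.1 = 70.4. At 10% loss, 70 × 0.9 = 63 remain. Keeping 64 allows a loss of 6 / 70 = 8.6%. The cost of one patient per group is 80.1 − 79.5 = 0.6 points of power.

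**The case against.** The strongest defence is that the word two-sided is a slip. One-sided 0.025 is the usual choice for non-inferiority, it agrees exactly with the 95% interval, and an ordinary two-sided P<0.05 agrees with both. On that reading only a label is wrong. This is the likeliest explanation, and n = 64 at a standardised distance of 0.50 fits it. But that fit is only suggestive, because the literal alpha also leads to 64 with an SD near 3.1. The printed text remains contradictory until it is corrected.

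The defence is also right about stronger readings that a reader might infer:

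- **That the trial falls short of 80% power because of the alpha conflict.** This would need 64 to be sized at one-sided 0.025 and then tested with a 97.5% interval. The Statistical analysis section plans a 95% interval, and no section plans a 97.5% one.
- **That the pilot difference was ignored, so that power is lower than claimed.** This needs an assumed SD of 4.0 and a true difference of zero. The section prints the 0.3-point difference just before the calculation, and SD 3.4 with that difference also gives 64.
- **That the type I error is uncertain by a factor of four.** The P<0.05 threshold follows a general list of tests and is not attached to the non-inferiority claim. The factor of four holds only if someone applies it to a one-sided P value.

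The dropout slip is a common rounding habit and is immaterial by itself.

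**Conclusion.** The alpha statement is wrong as written. The two sections give the primary non-inferiority claim nominal one-sided error rates of 0.0125 and 0.025, a twofold difference, and the missing SD prevents a reader from settling which was used for sizing. The Discussion's statement on power is not refuted by this. Provided that 64 was correctly computed under either reading of the sample-size section, and that its inputs hold, the 95% interval gives about 80% or about 87% power. With 63 evaluable per group the first figure becomes about 79.5%. Severity is moderate: the decision threshold of the primary claim needs one unambiguous statement, but neither the design nor the number of patients is undermined.

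**What to change.** 1. In both Sample size calculations and Statistical analysis, state a one-sided alpha of 0.025, with non-inferiority concluded if the upper limit of the two-sided 95% CI for the Cstat minus EIT difference in lung collapse is below 2 percentage points.
2. Say that the general P<0.05 threshold does not govern this comparison.
3. Print the SD and the true difference that were entered in the sample-size software, and confirm the alpha entered.
4. Keep 140 patients and restate what they deliver: 63 evaluable per group at 10% loss, or 64 at 8.6% loss. Recompute the power from the actual inputs; it is about 79.5% with 63 per group if 64 was sized at one-sided 0.025.

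The cost is a few restated sentences and figures. No patients are added, and the stated power may fall by about half a point.
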